### Data and Measurements

#### The Child Level

##### Physical activity

We will assess PA objectively over 7 consecutive days using the ActiGraph GT3X + accelerometer (John and Freedson, 2012), which is the most used and validated accelerometer in the field (De Vries et al., 2009; O’Brien et al., 2018). Children will be instructed to wear the accelerometer on the right hip 24 h per day, except during water activities (swimming, showering). Units will be initialized at a sampling rate of 30 Hz, and files will be analyzed at 1-s epochs using the KineSoft analytical software version 3.3.80 (KineSoft, Loughborough, United Kingdom) to correctly capture the lower and higher intensity levels (Aadland et al., 2018a, 2019). In all analyses, consecutive periods of ≥ 20 min of zero counts will be defined as non-wear time (Esliger et al., 2005; Cain et al., 2013). Results will be reported for the overall PA level [counts per minute (cpm)], as well as minutes per day spent sedentary (<100 cpm), in light PA (100–2295 cpm), in moderate PA (2296–4011 cpm), in vigorous PA (≥4012 cpm), and in MVPA (≥ 2296 cpm), determined using the previously established and validated Evenson et al. cut points (Evenson et al., 2008; Trost et al., 2011). As appropriate, sensitivity analyses will be conducted using the Pate et al. cut points (Pate et al., 2006).

In addition to the “standard” PA intensity profile, we will create a dataset having a higher resolution using 33 PA variables of total time (min/day) to capture movement in narrow intensity intervals throughout the spectrum; 0–99, 100–249, 250–499, 500–999, 1,000–1,499, …, 14,500–14,999, and ≥ 15,000 cpm. As shown previously (Aadland et al., 2018b; Nilsen et al., 2019a), this dataset will be used to investigate the PA signature associated with relevant outcomes.

PA during the whole day, week, and weekend days, as well as PA during care hours (08:30–15:30) and afternoon hours (15:30–23:59) on weekdays only, will be analyzed to specifically assess intervention effects during care hours and to assess possible compensatory behavior outside the preschool domain (Gomersall et al., 2013; Nilsen et al., 2019b). Data for a full day will be analyzed with wear-time requirements of ≥ 8 h/day and ≥ 3 weekdays + ≥ 1 weekend day, whereas ≥ 5 and ≥ 3 h/day of monitoring for ≥ 3 weekdays will be used as wear requirements for care hours and afternoons, respectively.

Screen time will be assessed using a parent questionnaire adapted from the Sunrise study protocol (Sunrise, 2020). Measurement properties of the questionnaire will be documented.

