##### Sleep

Children’s sleep will be assessed using 24 h accelerometry and a parent questionnaire. Accelerometry has been applied to assess sleep in multiple studies in preschoolers and older children (Galland et al., 2018), although procedures for assessment of sleep are less developed than for movement behaviors (Migueles et al., 2017). Most of these studies have applied wrist-worn accelerometers (Migueles et al., 2017; Galland et al., 2018), but there are ongoing efforts to assess and develop measurement properties of sleep for waist-worn accelerometry (Hjorth et al., 2012; Zinkhan et al., 2014; Barreira et al., 2015). There is currently no validated accelerometry-based sleep scoring algorithm for preschoolers (Migueles et al., 2017). We will therefore use the scoring algorithm by Sadeh et al. (1994), which is developed for assessment of sleep in children and youth, and incorporated by ActiGraph (ActiLife), as the starting point. However, since this algorithm was developed for wrist-worn accelerometers, using it with waist-worn accelerometers should be done with care since results are not directly comparable (Hjorth et al., 2012; Zinkhan et al., 2014). Alternative scoring protocols developed with or validated for waist-worn accelerometers, for example as suggested by Barreira et al. (2015), will therefore be used as appropriate, if improved measurement properties can be demonstrated in preschoolers.

In the questionnaire, adapted from the Sunrise study protocol (Sunrise, 2020), parents are asked to report children’s sleep duration (including nap time), when they go to bed, when they wake up, and whether these patterns are consistent. Furthermore, they will rate children’s sleep quality (1–7 scale). Measurement properties of the questionnaire will be documented.

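### The physical activity rules do not separate sleep from waking time, so movement-broken sleep is kept as wear and scored mainly as sedentary in the whole-day and afternoon analyses

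*Protocol article*

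**What the plan says.** The Physical activity section of the Protocol article (Data and Measurements, The Child Level) fixes these rules:

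- **Wear:** "Children will be instructed to wear the accelerometer on the right hip 24 h per day, except during water activities (swimming, showering").
- **Removal of time:** one rule, with general scope: "In all analyses, consecutive periods of ≥ 20 min of zero counts will be defined as non-wear time". Files are processed in 1-s epochs. No allowance for brief non-zero counts is stated for children; the staff rule does have one.
- **Outcomes:** overall counts per minute (cpm) and time by intensity. Sedentary time is reported as "minutes per day spent sedentary (<100 cpm"), with no condition that the child is awake. A finer set of 33 intensity variables starts with 0–99 cpm.
- **Windows:** "PA during care hours (08:30–15:30") and "afternoon hours (15:30–23:59) on weekdays only". The whole day is given no start or end hour.
- **Valid data:** at least 8 h/day on 3 weekdays and 1 weekend day for the full day; at least 5 h for care hours and 3 h for afternoons, on 3 weekdays.

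The Sleep section uses the same recordings: "sleep will be assessed using 24 h accelerometry and a parent questionnaire". It does not say that scored sleep is taken out of the activity data. It also concedes that no accelerometer sleep algorithm is validated for preschoolers and that the planned one was developed for wrist wear. The Analysis Plan makes child physical activity a secondary outcome.

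**The concern.** Nothing in these rules tells sleep from quiet waking time. A zero run shorter than 20 minutes is wear, and with 1-s epochs and no stated tolerance a single turn in bed ends a run. The minutes on either side of that turn then enter the data as wear below 100 cpm.

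Three results follow for the whole-day and afternoon analyses. Sedentary minutes and the 0–99 cpm variable rise, cpm falls because its denominator grows, and sleep helps a day or an afternoon meet its wear threshold. How much is retained depends on how restless the child's sleep is, so these variables partly measure night wear and restlessness. The afternoon window is the most exposed, and it is the one that the plan uses to look for compensation outside preschool.

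**Working it through.** The plan states no figure for sleep, bedtime or retained wear, so there is nothing to reproduce. The check is arithmetic on the stated windows. Bedtime, sleep length and movement rate are assumptions.

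**1. Share of the afternoon window after bedtime.** 15:30 to 23:59 is 509 min.
- Bedtime 19:30: 269 min remain, 269/509 = 53%.
- Bedtime 20:00: 239 min, 47%.
- Bedtime 21:00: 179 min, 179/509 = 35%.

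These shares are time exposed to the problem, before the zero-count rule acts. They are not the distortion itself.

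**2. Share of sleep that survives the zero-count rule.** If movements in sleep occur at random at L per hour, the share of sleep lying in zero runs shorter than 20 min is f = 1 − exp(−L/3) × (1 + L/3). This gives f = 0.045 at L = 1, 0.26 at 3, 0.59 at 6 and 0.91 at 12.

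**3. Effect on the outcomes.** Let S be sleep minutes in the window and A waking wear minutes, with sleep counts taken as about zero.
- Added wear, scored mainly as sedentary: f × S.
- Cpm relative to the waking value: A / (A + f × S).
- Waking minutes needed for a valid period: max(0, threshold − f × S).

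Afternoon, bedtime 20:00 (S = 239, A = 270, threshold 180 min):

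| Movements/h | Added min | Cpm ratio | Waking min needed |
|---|---|---|---|
| 1 | 11 | 0.96 | 169 |
| 3 | 62 | 0.81 | 118 |
| 6 | 141 | 0.66 | 39 |
| 12 | 217 | 0.55 | 0 |

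Whole day, 10 h of sleep (S = 600, A = 840, threshold 480 min):

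| Movements/h | Added min | Cpm ratio | Waking min needed |
|---|---|---|---|
| 1 | 27 | 0.97 | 453 |
| 3 | 156 | 0.84 | 324 |
| 6 | 354 | 0.70 | 126 |
| 12 | 546 | 0.61 | 0 |

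Example: at 3 movements per hour the whole-day ratio is 840 / (840 + 156) = 0.84.

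**4. Sensitivity and bounds.** At 3 movements per hour the afternoon ratio is 0.77 with bedtime 19:30 and 0.88 with bedtime 21:00; with 11 h of sleep the whole-day ratio is 0.82. If f = 0 there is no distortion. If f = 1 the added time is 239 min (afternoon) or 600 min (whole day).

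**5. What is not touched.** Retained sleep near zero counts adds no MVPA minutes; MVPA can change only through which days count as valid. The care-hours window holds no night sleep, so only daytime naps could enter it.

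**The case against.** The strongest reply is that the zero-count rule already does much of the work. Still sleep forms zero runs of 20 min or more and leaves both wear and sedentary time. That stands: a reader might infer that all sleep is counted as sedentary, and the rules do not support this. Only the share f is kept, and the documents do not give f.

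Second, a condensed article may leave the order of processing steps to a fuller document. This stands in part. For the same reason, a reader might infer that the same minutes are analysed both as sleep and as sedentary time, but the Sleep section does not say that scored sleep stays in the activity data. The 23:59 endpoint and the general scope of the single removal rule are, however, positive statements. Following them as written gives the misclassification.

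Third, a reader might infer bias between arms, since families are not blinded. The documents show no mechanism. Preschool staff deliver the intervention, and the same processing applies to both arms.

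Fourth, days with little waking wear pass as valid only if children take the device off by day and wear it at night. Nothing in the documents suggests that this is common, so the effect on valid-day selection is a possibility, not a finding.

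Finally, physical activity is secondary, and the plan has a separate care-hours window for effects during preschool. Both are true and limit the weight of the point.

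**Conclusion.** The point holds in a limited form. As written, the rules keep movement-broken sleep as wear and score it mainly as sedentary in the whole-day and afternoon analyses. The direction is clear: more sedentary time, lower cpm, and wear criteria that sleep can help to meet.

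The size is undetermined. Under the assumed 10 h of sleep, the loss in whole-day cpm runs from about 3% (1 − 0.97) to 39% (1 − 0.61). With a 20:00 bedtime, the afternoon loss runs from about 4% to 45%. Both ranges rest on random movements at 1 to 12 per hour and on full night wear.

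The likely consequence is added noise and dilution in secondary physical activity outcomes, most of all in the afternoon compensation analysis. The cognitive outcomes are not measured by these rules. The point should be fixed, but it does not threaten the trial's main comparison.

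**What to change.** Restrict the whole-day and afternoon activity analyses to a fixed waking window. State the morning hour at which the whole day opens and the evening hour at which both windows end. Apply the window before the non-wear and wear-time rules, and count only wear inside it towards the 8 h and 3 h criteria.

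As a sensitivity analysis, remove sleep by parent-reported bed and wake times or by accelerometer scoring. Neither should be the main rule: the Sleep section says that no algorithm is validated for this age group and that the questionnaire's measurement properties are still to be documented.

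The cost is reprocessing of files already collected, with no new data. Some days will become invalid, and some waking or sleep minutes will be misassigned at the edges of the window.

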##### Physical fitness and motor skills

The fitness assessment in the ACTNOW study is based on three items (handgrip strength, standing long jump, and speed-agility) from the Assessing FITness in PREschoolers (PREFIT) battery (Ortega et al., 2015). PREFIT is an adaptation of the ALPHA-Fitness: field-based fitness tests for the assessment of health-related physical fitness in children and adolescents, and have demonstrated good reliability in young children (Castro-Pinero et al., 2010; Artero et al., 2011; Ruiz et al., 2011). Hand-grip strength will be measured with a hand dynamometer with adjustable grip (TKK 5001 Grip A, analog model (Cadenas-Sanchez et al., 2016), measurement range 0–100; Takey, Tokio Japan), and a grip−span of 4.0 cm (Sanchez-Delgado et al., 2015). Lower body explosive strength will be measured using standing long jump, where children are instructed to jump as far as possible, measured in centimeters. Speed-agility will be assessed using a shuttle running test where children are instructed to run 4 × 10 m as fast as possible, measured in seconds.

To evaluate fundamental motor skills (FMS), we developed a test battery guided by the “Test of Gross Motor Development 3” (TGMD-3) (Ulrich, 2013, 2019). TGMD-3 is designed for children aged 3–10 years, and originally based on observation of children’s movements across 13 tasks within the two domains: locomotion (run, skip, slide, gallop, hop, and horizontal jump) and ball/object control (hereafter referred to as “object control”) (overhand throw, underhand throw, catch, dribble, kick, one-hand strike, and two-hand strike). We modified this test battery to reduce the participant and researcher burden, and at the same time cover the three main domains of FMS by including balance skills (Sun et al., 2010). We therefore included six movement items from the TGMD-3 battery (run, horizontal jump, hop, catch, overhand throw, and kick), in addition to three movement items within the balance domain (single leg standing, walking line forward, and walking line backward) from the Preschooler Gross Motor Quality Scale (PGMQ) proposed by Sun et al. (2010). The specific items were selected based on their relevance (e.g., some of the movement items in the TGMD-3, like the baseball strike and dribble, are less common and therefore less relevant in assessments of Norwegian children), and variety (e.g., including object control skills related to both hands and feet, and adding both static and dynamic balance tests) to broadly capture children’s skills within the three FMS domains. We have previously demonstrated good inter-rater reliability for this FMS battery (Nilsen et al., 2019a).

Children’s fitness and FMS will be evaluated in small groups (4–5 children) during preschool hours, in a safe environment with enough space to move freely. Each child performed each task twice, and skills will be completed in a standardized order, using approximately 40 min per group. The test teams consist of one instructor who provide a verbal description and demonstration of the required skill, while a separate assessor observe and score the performance. The physical fitness and FMS tests are administered and scored according to the TGMD-3 (locomotor and object control skills), PGMQ (balance skills), and PREFIT-protocols (hand grip strength, standing long jump, speed-agility). Briefly, each of the nine FMS movement tasks is described by three to four performance criteria, which is scored 0 or 1 if a criterion is absent or present, respectively. Scores are summed for each task and each domain.

##### Anthropometry and demography

We will assess children’s body mass, height, and waist circumference according to the PREFIT battery (Ortega et al., 2015). Body weight will be measured to the nearest 0.1 kg using an electronic scale (Seca 899, SECA GmbH, Hamburg, Germany), and height will be measured to the nearest 0.1 cm with a portable stadiometer (Seca 217, SECA GmbH, Hamburg, Germany). Body mass index (kg/m^2^) is calculated and children classified as normal weight, overweight, or obese based on criteria proposed by Cole et al. (2000). Waist circumference will be measured twice to the nearest 0.1 cm at the level of the umbilical zone. Demography includes the variables socioeconomic status (parents’ education and income), children’s and parents’ origins, children’s birth weights, parents’ weight status, and parents’ PAs, and they will be measured by parent questionnaires.

##### Sleep

Children’s sleep will be assessed using 24 h accelerometry and a parent questionnaire. Accelerometry has been applied to assess sleep in multiple studies in preschoolers and older children (Galland et al., 2018), although procedures for assessment of sleep are less developed than for movement behaviors (Migueles et al., 2017). Most of these studies have applied wrist-worn accelerometers (Migueles et al., 2017; Galland et al., 2018), but there are ongoing efforts to assess and develop measurement properties of sleep for waist-worn accelerometry (Hjorth et al., 2012; Zinkhan et al., 2014; Barreira et al., 2015). There is currently no validated accelerometry-based sleep scoring algorithm for preschoolers (Migueles et al., 2017). We will therefore use the scoring algorithm by Sadeh et al. (1994), which is developed for assessment of sleep in children and youth, and incorporated by ActiGraph (ActiLife), as the starting point. However, since this algorithm was developed for wrist-worn accelerometers, using it with waist-worn accelerometers should be done with care since results are not directly comparable (Hjorth et al., 2012; Zinkhan et al., 2014). Alternative scoring protocols developed with or validated for waist-worn accelerometers, for example as suggested by Barreira et al. (2015), will therefore be used as appropriate, if improved measurement properties can be demonstrated in preschoolers.

In the questionnaire, adapted from the Sunrise study protocol (Sunrise, 2020), parents are asked to report children’s sleep duration (including nap time), when they go to bed, when they wake up, and whether these patterns are consistent. Furthermore, they will rate children’s sleep quality (1–7 scale). Measurement properties of the questionnaire will be documented.

##### Socioemotional health, self-regulation, executive function, and learning

We will adapt several validated tests to examine different aspects of socioemotional health, self-regulation, executive functions, and learning. Yet, there exists little agreement on the optimal measures and their configuration for capturing important aspects of early cognitive development (Garon et al., 2008; Howard and Melhuish, 2017).

To assess **socioemotional health,** we will ask the teachers to fill out the Strengths and Difficulties Questionnaire (SDQ) for each child. The SDQ is a brief measure of psychosocial strengths and problems in 3- to 16-years-old children. The SDQ asks about 25 attributes (10 positive, 14 negative, and 1 neutral) divided between five subscales of five items each: (*1) Emotional Symptoms Scale; (2) Conduct Problems Scale; (3) Hyperactivity Scale; (4) Peer Problems Scale;* and (*5) Prosocial Scale*. All but the last scale are also summed to give a total difficulties score. SDQ uses a 3-point Likert scale to indicate the extent to which each attribute applies to a child (“not true,” “somewhat true,” or “certainly true”) (Goodman, 1997, 2001). The construct validity of the SDQ has been demonstrated in several studies (Goodman, 2001; Stone et al., 2010; Mieloo et al., 2012), and the reliability and validity of the SDQ has been shown to be satisfactory (Goodman, 2001; Stone et al., 2010). The teacher version of the SDQ has shown both higher internal consistency and test-retest reliability compared to the parent version for preschool and schoolchildren (Stone et al., 2010; Mieloo et al., 2012).

**Self-regulation** will be assessed both by teacher-report and a structured observation (direct measure) of a child’s performance. Teachers will be asked to fill out the 33-item Child Self-regulation and Behavior Questionnaire form from the Early Years Toolbox (EYT) (Howard and Melhuish, 2017). The Child Self-regulation and Behavior Questionnaire generates subscales on cognitive, behavioral, and emotional self-regulation, in addition to sociability, prosocial behavior, externalizing and internalizing problems, which overlaps with the SDQ. Each item asks the teacher to evaluate the frequency of target behaviors of each child on a scale from 1 (not true) to 5 (certainly true). The subscales of the questionnaire have been shown to be reliable in preschoolers (Howard and Melhuish, 2017).

The directly assessed Head-Toes-Knees-Shoulders task assesses the ability of a child to use and integrate the executive functions to control and direct actions, pay attention, and remember instructions (Cameron Ponitz et al., 2008; Ponitz et al., 2009; Cameron et al., 2012; von Suchodoletz et al., 2013). To respond correctly, the task requires that children listen to instructions, remember and execute gross motor movements in relation to directions, and inhibit pre-potent incorrect responses. In the first part (10 items), two rules are paired: “touch your head” with “touch your toes.” In the second part (10 items), two more paired rules are added: “touch your knees” with “touch your shoulders” (Ponitz et al., 2009). Children are instructed to perform the opposite of the dominant response. Hence, the command to “touch your head” requires the children to touch their toes, and the command to “touch your shoulders” requires the children to touch their knees. If the children reach a minimum performance threshold of 4 points on both of these levels (2 points are given for a correct response, and 1 point for a self-corrected response), a third section (10 items) will be given, where the paired rules are switched (i.e., head goes with knees and shoulders go with toes) (McClelland et al., 2014). Instructions will be given verbally in a fixed order, without feedback. Preceding each level, four practice trials and up to three attempts on each are provided to familiarize with the test (Cameron Ponitz et al., 2008). The Head-Toes-Knees-Shoulders task is quick to administer, requires few materials, and has shown construct validity in European samples (von Suchodoletz et al., 2013).

We will assess all three key **executive functions** identified by Miyake et al. (2000): inhibition, working memory, and cognitive flexibility. These three executive functions will be measured using assessments from the iPad-based EYT (Howard and Melhuish, 2017). EYT has shown good reliability, convergent validity with existing measures, and developmental sensitivity (Howard and Melhuish, 2017). The EYT is developed for preschool children (which contrasts the majority of measures that are modified adult versions), with emphasis on being (a) developmentally appropriate, (b) developmentally sensitive, (c) brief, (d) engaging, (e) technologically dynamic without introducing effects of technological expertise, and (f) internationally applicable. The EYT is available on iTunes App Store. We embedded a Norwegian version to ensure its application in the children’s native language.

To measure the visual-spatial working memory we will use *“The [name] task”* (Howard and Melhuish, 2017). In this task, children are asked to remember spatial locations of “sticker/s” that are placed on [name] body. The children then, after a brief retention interval, tap the spatial locations where they believe the stickers were on [name]. The test trials increase in difficulty by increasing the number of stickers on [name] body (progressing from one to eight stickers). All trials progress as follows: (a) [name] presents with *n* colored stickers for 5 s, (b) the screen is blank for 4 s, and then (c) an image of [name] without stickers – along with an auditory prompt to recall where the stickers were – is presented until the child’s response is complete. The task continues until completion, or until failure on all three trials at the same level of difficulty. Children are given instruction and three practice trials to familiarize them with task requirements prior to administration of test trials. Working memory will be indexed by a point score calculated as follows: starting from Level 1, 1 point for each passed level (at least two of the three trials performed accurately), plus 1/3 of a point for all correct trials thereafter (Howard and Melhuish, 2017).

To measure inhibition, we will use *“The Go/No-Go task”* (Howard and Melhuish, 2017). In this task, the children are asked to catch the fish (Go trial) by tapping the screen when they see a fish, and to avoid the shark (No-Go trial) by not tapping the screen when they see a shark. Because the majority of the stimuli are Go trials (80% fish), this generates a pre-potent response to tap the screen, requiring the children to inhibit this response (not tap) in No-Go trials (20% sharks). The children are given instructions and practice to familiarize with requirements as follows: go instructions, followed by five practice Go-trials; No-Go instructions followed by five practice No-Go trials; combined Go/No-Go instructions followed by a mixed block of 10 practice trials (80% Go-trials); and a recap of instructions. Feedback in the form of auditory tones is provided on all practice trials. The task proceeds with 75 stimuli divided evenly in three 1-min test blocks (each separated by a short break and a reiteration of instructions). Blocks always begin with a Go stimulus, and no more than two successive trials are No-Go stimuli. Each trial involves a presentation of an animated stimulus (i.e., fish or shark) for 1,500 ms, separated by a 1,000 ms interstimulus interval. The outcome is an impulse control score that is the product of proportional Go and No-Go accuracy (Howard and Melhuish, 2017).

Cognitive flexibility/shifting will be measured by the “*The Card Sorting task.”* This task asks the children to sort red rabbits and blue boats by either color or shape, into two locations (identified by a blue rabbit and a red boat). As the card sorting rules alternate, the children must switch between rules. The children are first given a demonstration trial and two practice trials. Then they are asked to sort stimuli by one dimension for six trials (with the same stimulus never presented more than twice in a row). In the subsequent post-switch phase, children are required to sort by the other sorting dimension, as prompted by auditory instructions preceding post-switch test trials. If the child correctly sorts at least five of the six pre- and post-switch stimuli, they proceed to a border phase of the task. In this phase, children are required to sort by color if the card has a black border or sort by shape if the card has no black border, preceded by a demonstration trial and two practice trials. This sorting rule is reiterated prior to all test trials. Scoring represents the number of correct sorts after the pre-switch phase (Howard and Melhuish, 2017).

As a proxy for **learning** we will use “*The Expressive Vocabulary”* for language development (Howard and Melhuish, 2017) and *“The Numbers task”* for early math skills (manuscript not published), both from the EYT. Both measures have shown good convergent validity and reliability (Howard and Melhuish, 2017). In the Expressive Vocabulary task, consisting of 54 items, children are asked to verbally produce a correct label for the depicted nouns and verbs. The administrator records the response directly into the iPad app (correct/not correct). In cases of an incorrect label, the administrator will prompt the children by asking, “What else might this be called?” until either a correct production or an indication that the child is unable to produce the target word. A six-item failure stop rule will be used to minimize administration time. Expressive Vocabulary performance will be scored as overall accuracy (Howard and Melhuish, 2017).

The Numbers task consists of 79 items pertaining to numerical concepts (e.g., many), spatial and measurement concepts (e.g., tallest), counting subset (e.g., counting dogs interspersed with cats), matching digits and quantities (e.g., understanding the correspondence between: spoken number *two*, the digit *2*, and its corresponding quantity), number order (e.g., identifying the missing number in a number line), ordinality (e.g., identifying higher/lower numbers), cardinality (e.g., identifying what is 1st, 2nd, etc.), subitizing (e.g., a rapid appraisal of quantities as having more or less), patterning (e.g., identifying and completing a pattern), and numerical word problems and equations. In this task, children respond to each item either by tapping the iPad screen or verbally answer auditory questions in the app (which is recorded directly in the app by the administrator). The app integrates automated start rules based on the age of the child, and stop rules after five consecutive incorrect responses.

